### Endpoints

#### Primary Endpoints

(1)Prevalence of anxiety and/or depression at baseline.(2)Change in prevalence of combined anxiety and depression from baseline.(3)Change in proportion of those who report signs and symptoms, or evidence consistent with COVID-19 from baseline to the end of study.

#### Secondary Endpoints:

(1)Prevalence of combined anxiety, depression, or sleep disorder at baseline.(2)Prevalence of those with sleep disorders at baseline.(3)Change in prevalence of anxiety, depression, and sleep disorder from baseline to the two follow-up time points.(4)Change in prevalence of burnout from baseline to the two follow-up time points.(5)Proportion of those with low mental wellbeing at baseline and follow-up.(6)Change in behavioral habits such as smoking and alcohol intake from baseline to follow-up.(7)Proportion of those who report suspected or confirmed diagnosis of COVID-19.(8)Proportion of those who report their working conditions adversely affecting their personal relationships.

## Definitions of Various Endpoints: How We Will Assess Them

### Psychological

#### Presence of Anxiety

The presence of anxiety is screened using the Generalized Anxiety Disorder-7 (GAD-7) assessment. This is a validated self-administered patient questionnaire used as a screening tool and severity measure for generalized anxiety disorder (GAD). The minimum score is 0 and maximum score 21. The following scoring system will be employed (Kroenke et al., 2001):

*Mild: 5–9; Moderate: 10–14; Severe: >15*.

A score of ≥10 has a sensitivity of 89% and specificity of 82% for GAD. The GAD-7 scoring tool has also been shown to have acceptable sensitivity and specificity for other types of anxiety disorders such as panic disorder, social phobia, and post-traumatic stress disorder (sensitivity 68% and specificity 88% with a cut off score of 10, for any anxiety disorder).

#### Presence of Depression

The presence of depression is screened using the Patient Health Questionnaire-9 (PHQ-9). This is a validated nine-item questionnaire designed to screen for depression, often used in a primary care setting. A PHQ-9 score of ≥10 has an 88% sensitivity and specificity for major depression (Spitzer et al., 2006). The severity of depression is rated as follows:

None: 0–4; Mild: 5–9; Moderate: 10–14; Moderately severe: 15–19; Severe: 20–27.

#### Sleep-Related Issues

Sleep related issues are assessed through the Insomnia Sleep Index (ISI). This is a validated seven-item self-report questionnaire assessing the nature, severity and impact of insomnia, evaluating aspects such as severity of sleep onset, sleep maintenance, sleep dissatisfaction, and interference of sleep difficulties (Tennant et al., 2007). The score categories are as follows (Bastien et al., 2001):

0–7: No clinically significant insomnia; 8–14: Sub threshold insomnia; 15–21: Clinical; insomnia (moderate severity); 22–28: Clinical insomnia (severe).

#### “Mental Wellbeing”

Mental wellbeing is assessed using the Short Warwick-Edinburgh Mental Wellbeing Scale (SWEMWBS). This has been validated for use in the general population and facilitates monitoring mental wellbeing in the general population (Tennant et al., 2007):

Scores of 7–17 suggest probable depression or anxiety; Scores of 18–20 suggest possible depression or anxiety. Scores range from 7 to 35. Higher scores indicate higher positive mental wellbeing.

#### Burnout

Burnout was assessed using single Item measures for Emotional Exhaustion and Depersonalization (West et al., 2009). This 2-Question summative score has been shown to be correlated with two items from the Maslach Burnout Inventory (Li-Sauerwine et al., 2020).

### Lifestyle and Physical Health

#### Behavioral Habits, Such as Smoking, Alcohol Intake and Recreational Drug Use

Self-reported measures through responses to customized questions developed the research team (see Supplementary Data Sheet 1).

#### Diet and Physical Activity

Customized questions on diet, exercise levels and de-stressing activity.

#### Physical Health

##### Evidence consistent with probable diagnosis of COVID-19

This is self-reported and is assessed through questions regarding the presence of symptoms with the presence of either a self-reported positive test, or self-isolation for 7 days or more.

Customized questions on symptoms of COVID-19, swab and antibody status and days of absence/sick leave taken and potential need for hospitalization.

### Relational and Support

#### Social/Relational

Customized questions on living arrangements and impact of the pandemic on personal relationship.

#### Concerns Related to Workplace and Support

Customized questions developed by the research team to assess self-reported responses to workplace related concerns including availability of support at work.

## Study Questionnaire and Dissemination

This will be achieved through a wide distribution of the electronic survey to HCPs and non-HCP controls. We will seek endorsement and support from professional societies and associations in the United Kingdom and other parts of the world to disseminate this widely. Distribution networks that will be considered include network email distribution lists and relevant social media platforms.

We expect to have a larger distribution of the questionnaire in the United Kingdom, but we are aiming at achieving an international cohort of participants. Within the United Kingdom, dissemination will be through different NHS Trusts, geographically distinct deaneries involving with overseeing medical training, scientific and medical societies and universities. On an international level we will involve international medical and allied health scientific societies and associations.

There will be an invitation to join the study including an explanation of the reasons of the survey. Any participant taking part in the survey based on the brief description of the study will be deemed to have consented for the study, and no other consent will be required. This cross-sectional survey will include basic information about the participant including demographics, living circumstances, education level and pre-existing physical and mental health conditions. It will also include questions regarding work experience and profession, work circumstances and exposure to COVID-19. Table 1 provides a summary of the aspects assessed and the tools used.

**TABLE 1 T1:** Study variables and respective assessment tools.

Variables	Assessment Tool
***Psychological***	
1. Anxiety	Generalized Anxiety Disorder-7 (GAD-7)
2. Depression	Patient Health Questionnaire-9 (PHQ-9)
3. Sleep-related issues	Insomnia Sleep Index (ISI)
4. “Mental wellbeing”	Short Warwick-Edinburgh Mental Wellbeing Scale (SWEMWBS)
5. Burnout	Abbreviated 2-Question Summative Score
***Lifestyle and physical health***	
6. Behavioral habits (smoking, alcohol intake and recreational drug use)	Customized questions on cigarette smoking and vaping status, alcohol and recreational drug use.
7. Diet and physical activity	Customized questions on diet, exercise levels and de-stressing activity
8. Physical health	Customized questions on symptoms of COVID-19, swab and antibody status and days of absence/sick leave taken or potential need for hospitalization
***Relational and support***	
9. Social/relational	Customized questions on living arrangements and personal relationship
10. Concerns related to work place and support	Customized questions regarding concerns related to workplace and available work-based support

Comparing Groups 1 and 2 with Group 3 allows us to study the effect of a high-risk working environment alone, whether in a patient-facing (Group 1) or non-patient facing role (Group 2), on physical and psychological health. Group 3 may also function as a control group for confounders such as education level and living conditions (external control).

We aim to structure each of the questionnaires such that most of these questions can be answered in no more than 20 min. We will try to incorporate strategies such that relevant sections (rather than the whole) survey can be completed in multiple sittings with previous responses being saved.

## Patient and Public Involvement

As the study is aimed at HCPs, hospital workers, and academic staff, we have consulted with a range of different workers from these groups in refining the research questions, designing the survey and planning the follow-up.

### Procedure for Collecting Data

Data will be collected directly from the web-based survey platform^2^ using pre-defined questions using a combination of Likert scale, one of many tick options and free text etc. Participants will be free to withdraw (actively or by ceasing to complete any questionnaires at any time). Data collected up to the point of no further completion, or withdrawal will be kept for data analysis.

## End of Study Definition

The end of study definition is hierarchical based on collection of completed surveys from *n* > 400 from group 4 AND *n* > 80 from group 5 and 6. If not achieved, then at the end of 12 months from study opening.

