##### Follow-up study

All participants consenting for follow-up will be sent further questionnaires after 6-weeks (up to 8-weeks) and 4-months (up to 6-months), from date of completion of the baseline questionnaire, to assess for change from baseline. To improve the uptake, we will also send weekly reminders (no more than 3) to those who have not completed the survey at first request. We expect that about 60% from each of the three baseline groups will agree to take part in the follow-up study, and about two-third of those will respond to the follow-up surveys.

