### Method of Analysis

We will use the STATA 15 statistical software for analysis. Chi-square test will be used to compare the difference in prevalence of anxiety, depression and other variables between the groups at baseline. We will evaluate for changes in proportion of those outcomes at baseline to the end of the study using paired McNemar test. We will use logistic regression to assess the factors at baseline related to development of physical symptoms, overall, and in the HCPs group alone. Data will be described using appropriate descriptive statistics.

We will collect information for potential confounding factors such as age, gender, education level, and health conditions from both HCPs and their controls and adjust for these in the analysis. For all validated tools, we will use appropriate and previously published cut-offs to categorize them. For example, for the primary end point of anxiety, we will use the cut-off related to moderate anxiety, but also do a sensitivity analysis using cut-off using “mild” anxiety definition. Similar and consistent strategy will be followed for other validated tools. We will perform logistic regression for binary outcomes, such as those listed in our primary and secondary outcomes, after adjusting for pre-defined confounders including age, gender, and years of education. The choice of these *a priori* confounder is based on the significant association that exists for most of the study outcomes. We have also adjusted for time since the self-identified peak of the pandemic as this will impact on outcomes such as anxiety and depression. However, for the outcome of developing COVID-19 infection and change in prevalence of COVID-19 infection, we will also adjust for pre-existing medical conditions.

We will also stratify HCPs according to their roles (doctors, nurses, pharmacists, healthcare assistants etc.), and will evaluate and compare the endpoints by respective roles. Comparison between HCPs from the United Kingdom and outside will be undertaken adjusting for the self-identified peak of the pandemic in that region. We also will assess whether the years of experience (as a categorical variable) has any impact on the measured outcomes.

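### The end of study is set by a survey count not tied to a survey round, although change analyses use it as their time point, and the plan's own retention does not meet the count at minimum enrolment

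*Protocol article*

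**What the plan says.** Protocol article, End of Study Definition: "The end of study definition is hierarchical based on collection of completed surveys", with more than 400 required from Group 4 (the follow-up cohort of patient-facing staff) and more than 80 "from group 5 and 6. If not achieved, then at the end of 12 months from study opening".

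Three other parts of the article bear on this rule.

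- **Follow-up study.** Questionnaires go out at 6 weeks (accepted to 8 weeks) and at 4 months (accepted to 6 months) from each participant's own baseline. On agreement to follow-up, the section writes: "We expect that about 60% from each of the three baseline groups will agree to take part in the follow-up study". Its expectation for response among the people who agree is a separate, second step: "about two-third of those will respond to the follow-up surveys".
- **Primary Endpoints and Method of Analysis.** Endpoint 3 is a change "from baseline to the end of study". Endpoint 2 is a change from baseline with no end time named. Endpoint 1 is measured at baseline only. The McNemar test is applied to "changes in proportion of those outcomes at baseline to the end of the study".
- **Sample Size.** Half of the 800 healthcare professionals are assumed to join the cohort, giving 400 with no further non-response. That cohort supports 80% power for 20% versus 32.3% at the end of the study, and a separate statement about change from baseline in the 160 with symptoms at baseline.

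**The concern.** The phrase for the end of the study does two jobs. Operationally it says when data collection stops. In endpoint 3, the McNemar analysis and the power statements it is also the time at which the outcome is measured. The only definition the article gives is a count with no survey round attached, and it does not say whether the 80 is per control group or combined.

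Two things are at stake. First, the length of follow-up behind the primary change analyses could depend on how well recruitment went: a successful study could stop before late responders to the 4-month questionnaire have returned it. Second, the count and the power statement both assume a cohort of about 400, which the article's own response expectations do not produce at minimum enrolment.

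**Working it through.** **Inputs.** Minimum enrolment 800 / 125 / 125 (Sample Size). Agreement 60%, response two-thirds (Follow-up study). Cohort of 400, of whom 160 have baseline symptoms; 20% versus 32.3%; two-sided 0.05 (Sample Size). Opening 24 July 2020 and about 6 weeks of recruitment (Study Design; Baseline). Thresholds >400 and >80, fallback 12 months (End of Study Definition).

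**1. Reproducing the stated power.** I read the two groups as those with and without baseline symptoms, 160 and 400 − 160 = 240. This split is inferred. With a normal approximation and pooled variance under the null:

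- pooled proportion = (160 × 0.323 + 240 × 0.20) / 400 = 0.2492
- null SE = √[0.2492 × 0.7508 × (1/160 + 1/240)] = 0.0441
- alternative SE = √[0.323 × 0.677/160 + 0.20 × 0.80/240] = 0.0451
- power = Φ[(0.123 − 1.96 × 0.0441) / 0.0451] = 79.1%

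With the two rates swapped between the groups it is 78.0%. The stated 80% is reproduced to within 2 points.

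**2. Expected follow-up on the plan's own retention.** Net yield = 0.60 × 2/3 = 40%.

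- Group 4: 800 × 0.40 = 320, against >400. Treating responses as independent at 40%, the chance of passing 400 is about 4 × 10⁻⁹.
- Each control group: 125 × 0.40 = 50. Only 125 × 0.60 = 75 would agree at all, so >80 per group is out of reach at minimum enrolment even with full response.
- Controls combined: 250 × 0.40 = 100, against >80; probability about 0.99.
- The Sample Size assumption gives 800 × 0.50 = 400 exactly, which is still not more than 400.

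**3. Power with the cohort that is expected.** 40% of 320 is 128, leaving 192. The same formula gives SEs of 0.0494 and 0.0504, and power 69.9% (68.3% with the rates swapped). If the two groups are instead 400 staff against 125 controls (half of 250), the plan's figure comes out at 77.0% to 79.7%. At 320 against 100 it is 66.8% to 71.0%. On either reading, power is roughly 70%.

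**4. When the count can be met.** Group 1 enrolment needed for an expected 401 responders: 401 / 0.40 = 1,002.5, so about 1,003. The probability of passing 400 is about 0.49 at 1,000, 0.89 at 1,050 and 0.99 at 1,100. The control count must be met as well. Combined, it is expected to be met at minimum enrolment; per group it needs 81 / 0.40 = 202.5, so about 203 in each.

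**5. Calendar, if recruitment closes exactly 6 weeks after opening.**

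- First 6-week survey due 4 September 2020; last 8-week limit 30 October 2020 (week 14).
- First 4-month survey due 24 November 2020 (week 17.6); last one due 4 January 2021 (week 23.4).
- Last 6-month limit 4 March 2021 (week 31.9).
- Fallback 24 July 2021, 142 days or about 20 weeks after that limit.

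If 6-week surveys count, the rule can be met by week 14, before any 4-month survey is due. If only 4-month surveys count, it cannot be met before week 17.6, but with enough enrolment it can be met before week 31.9.

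**The case against.** The strongest defence is the fallback: "If not achieved, then at the end of 12 months from study opening". If the count is missed, the study runs about 20 weeks past the last 6-month limit and every window closes. This stands. A reader might infer that an unreachable count is itself harmful, or that it leaves the study without an end; neither follows. The shortfall also applies only at the minimum of 800, which is a floor with no cap, and for the controls only if 80 is per group.

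Second, closure before any 4-month survey needs three things together: 6-week surveys counting, 80 being combined, and Group 1 above about 1,003. The article states neither of the first two. It sends both questionnaires to everyone who consents, and secondary endpoints 3 and 4 call for both follow-up times, which suggests that completed follow-up was meant. This also stands: week 14 is a possibility left open by the wording, not the plan's evident intention. The milder version, stopping partway through the 4-month wave, does not need 6-week surveys to count.

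Third, a condensed article may leave to the full protocol which round counts. That is fair for the operational detail alone. It does not cover a time point for a primary endpoint that rests on a definition the article does give, or three retention figures in the same article that disagree.

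**Conclusion.** The point holds in limited form. The end of study is defined by a count with no survey round, and that end is the outcome time for primary endpoint 3, the McNemar analysis and the follow-up power statements. Endpoint 2 names no time of its own, so it depends on those sections. Endpoint 1 is unaffected.

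- **At minimum enrolment:** about 320 are expected in Group 4 against more than 400. The fallback protects the timing. The cost is power of roughly 70% rather than 80% for 20% versus 32.3%.
- **Above about 1,003 in Group 1, with the control count met:** the study can end before the last 4-to-6-month window closes and cut off late responders. Under the least favourable reading it can end by about week 14.

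A reader might also infer that the analysis would mix 6-week and 4-month outcomes. That does not fit closure at week 14, when no 4-month data exist, and the documents do not establish it.

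The figures assume a 40% yield applying to each round, independent responses, recruitment of exactly 6 weeks, and the inferred group split in the power statement. The alternative split gives nearly the same power.

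**What to change.** 1. Define the end of study as closure of the last enrolled participant's 4-month (up to 6-month) window. The 12-month date can remain as an outer limit.
2. State that the end of study in primary endpoints 2 and 3 and in the McNemar analysis means each participant's 4-month questionnaire.
3. Keep the 400 and 80 only as follow-up completion targets, and say whether 80 is per control group or combined.
4. Use one retention assumption in Follow-up study, Sample Size and End of Study Definition, and restate the end-of-study power from it. At a 40% yield, either report about 70% for 20% versus 32.3% or raise the Group 1 minimum: 400 / 0.40 = 1,000 for an expected cohort of 400. If the comparison is with controls, 125 / 0.40 = 312.5, so about 313 controls in all would also be needed.

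Items 1 to 3 change wording only and add no data collection: everyone who consents to follow-up is already due the 4-month questionnaire, and its last window closes about 20 weeks before the fallback date. Item 4 costs a slightly less favourable stated power, or more recruitment if the sponsor prefers to keep 80%.

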## Statistical Considerations

### Sample Size

We aim to collect data from minimum of 800 HCPs, and minimum of 125 non-patient facing HCPs and 125 non-HCPs (total sample size of 1050). If minimum of 40% of HCPs report primary outcome (combined either depression and/or anxiety symptoms) compared with a maximum of 30% non-HCPs/non-patient facing HCPs, we will have just of over 80% power to detect significant difference using two-sided type 1 error at 0.05.

Assuming that only 50% of these HCPs agree to be a part of a cohort survey (*n* = 400), we will have at least 40% (*n* = 160) who have reported either depression or anxiety. We will have 80% power to detect around 12% difference in the two groups in reported physical symptoms (20% vs. 32.3%), or prevalence of depression and/or anxiety at the end of the study. We will also have about 80% power at two-sided alpha set at 0.05 to detect difference of 15% between baseline and the end-of study for all the primary and secondary objectives, amongst those who have reported anxiety or depression symptoms at baseline (*n* = 160). In the other arm, we have enough power to detect smaller changes from baseline.

Our assumptions here are based on most conservative estimates. If we are able to recruit more than the minimum numbers, our power will improve substantially, and we will be able to detect smaller differences too.

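### The follow-up power counts every agreeing HCP as analysed (n = 400), although the protocol's own response forecast gives 320, and the 12-point claim does not carry over to depression/anxiety

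*Protocol article*

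**What the plan says.** Under Sample Size, minimum enrolment is "minimum of 800 HCPs, and minimum of 125 non-patient facing HCPs and 125 non-HCPs". The baseline claim is "just of over 80% power to detect significant difference using two-sided type 1 error at 0.05", for 40% of HCPs against 30% of controls with depression and/or anxiety symptoms.

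The follow-up claim begins "Assuming that only 50% of these HCPs agree to be a part of a cohort survey", which gives n = 400. From this the section states 80% power for a "12% difference in the two groups in reported physical symptoms (20% vs. 32.3%), or prevalence of depression and/or anxiety" at the end of the study. It then takes 40% of the 400 (n = 160) as having baseline symptoms and claims about 80% power for a 15-point change from baseline in that subgroup. It concludes: "Our assumptions here are based on most conservative estimates". The Abstract repeats the 50% assumption and the 12-point claim.

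The Follow-up study section has a different forecast: "about 60% from each of the three baseline groups will agree to take part in the follow-up study, and about two-third of those will respond".

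The End of Study Definition sets a count: "The end of study definition is hierarchical based on collection of completed surveys from" more than 400 participants in group 4 and more than 80 from groups 5 and 6. Failing that, the study ends 12 months after opening.

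**The concern.** Agreeing to follow-up and returning the follow-up questionnaire are two steps, and the protocol forecasts both. The power calculation applies only the first and uses the agreeing number as the analysed number. Its 50% agreement is lower than the 60% forecast, which makes it look cautious. Without the response step, however, it ends at 400 HCPs where the forecast ends at 320.

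A second, independent problem is the base rate. A 12-point difference needs more participants at 30% than at 20%, because the binomial variance is larger. The figure is worked out at 20% for physical symptoms and then claimed for an outcome that the same section puts at 30% in controls.

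Both errors overstate the power of the follow-up comparisons. A reader who trusts 80% would take a null result at follow-up as stronger evidence of no difference than it is.

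**Working it through.** **Inputs**
- Sample Size: two-sided alpha 0.05; minimum enrolment 800 / 125 / 125; 50% agreement; 20% vs 32.3% for physical symptoms; 30% depression/anxiety in controls.
- Follow-up study: 60% agreement, two-thirds response.

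**Numbers analysed**
- As used: 0.50 × 800 = 400 HCPs. The same fraction of the pooled controls is 0.50 × 250 = 125.
- As forecast: 0.60 × 2/3 = 0.40. HCPs: 0.40 × 800 = 320. Each control group: 0.40 × 125 = 50, so 100 pooled.

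**Formula** (normal approximation, pooled variance under the null)

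Power = Φ[(|p1 − p2| − 1.96 × s0) / s1], where s0 = √[p̄(1 − p̄)(1/n1 + 1/n2)], s1 = √[p1(1 − p1)/n1 + p2(1 − p2)/n2], and p̄ is the weighted mean rate.

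The protocol does not say which two groups are compared. Two readings fit: (a) HCPs with vs without baseline symptoms, 160 vs 240; (b) HCPs vs pooled controls, 400 vs 125.

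**Reproducing the plan's figures**
- Baseline, 800 vs 250, 40% vs 30%: 82.2%. This agrees with the plan.
- Follow-up, reading (a), 32.3% in the 160: s0 = 0.0442, s1 = 0.0451; (0.123 − 0.0865)/0.0451 = 0.81; power 79.1%.
- The other readings and directions are in the table. All lie within about 3 points of the stated 80%.

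**Correction 1: 40% response, rates unchanged (20% vs 32.3%)**

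| Comparison | Higher rate in | Power at n = 400 | Power at n = 320 |
|---|---|---|---|
| (a) with vs without baseline symptoms: 160 vs 240; 128 vs 192 | with symptoms | 79.1% | 69.9% |
| (a) | without symptoms | 78.0% | 68.3% |
| (b) HCPs vs pooled controls: 400 vs 125; 320 vs 100 | HCPs | 77.0% | 66.8% |
| (b) | controls | 79.7% | 71.0% |

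Example, 320 vs 100 with the higher rate in HCPs: s0 = 0.0522, s1 = 0.0478; (0.123 − 0.1023)/0.0478 = 0.43; power 66.8%.

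From a 20% base, the difference detectable with 80% power at n = 320 is 13.9 to 14.4 points across these four cases. At n = 400 it is about 12.4 to 12.8.

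**Correction 2: base rate for depression/anxiety**

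The 30% is a control rate, so only reading (b) applies. The protocol gives no follow-up rate for HCPs on this outcome. I assume the same 12.3 points on top of 30%, that is 42.3% in HCPs.
- 400 vs 125: s0 = 0.0501, s1 = 0.0479; (0.123 − 0.0981)/0.0479 = 0.52; power 69.8%.
- 320 vs 100: s0 = 0.0560, s1 = 0.0535; (0.123 − 0.1097)/0.0535 = 0.25; power 59.8%.
- Detectable difference with 80% power: 13.9 points at 400 vs 125, and about 15.5 points (15.6) at 320 vs 100.

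**Knock-on to the 15-point paired claim**

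The subgroup becomes 0.40 × 320 = 128, not 160. McNemar power = Φ[(d√n − 1.96√s)/√(s − d²)], with d = 0.15 and s the total discordance. The protocol does not state s, so a range is shown.

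| Discordance s | n = 160 | n = 128 |
|---|---|---|
| 0.30 | 94.1% | 88.2% |
| 0.40 | 85.8% | 77.2% |
| 0.45 | 81.4% | 72.1% |
| 0.50 | 77.0% | 67.4% |

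**End-of-study count**

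At 40% response, more than 400 completed surveys in group 4 needs more than 400/0.40 = 1,000 HCPs recruited. The forecast at minimum enrolment is 320.

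**The case against.** The strongest reply is that 800 is a floor. The protocol hopes to exceed it, and 1,000 HCPs at 40% response would give the 400 that was assumed. That is true, but the Sample Size section presents its 80% as holding at the minimum and calls its assumptions the most conservative.

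It can also be said that 50% agreement is below the forecast 60%, so the assumption is cautious. That holds for agreement alone; the defect is the missing response step.

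Third, 42.3% appears nowhere in the protocol. This stands: it is an assumption built on the stated 30%, and the second correction should be reported apart from the first. A reader might otherwise merge them and infer that the stated 80% is simply 60-71%. The documents do not support that. For the rates actually stated, the forecast response gives 67-71%.

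Two other stronger readings also fail. One is that this is the only power statement behind the change-from-baseline primary endpoints. The 15-point paired claim bears on them more directly, although it rests on the same uncorrected count. The other is that the end-of-study rule will necessarily run to 12 months and should be replaced. That default follows only at minimum recruitment. Questionnaire times are fixed from each participant's own baseline, and about 6 weeks of recruitment plus a 6-month window ends before 12 months, so the administrative rule neither moves the assessments nor loses data.

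Finally, overstated power biases no estimate or test. That is correct; what is affected is what the study may claim it can detect.

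**Conclusion.** The point holds as two separate corrections. First, the follow-up power uses 400 analysed HCPs where the protocol's own forecast gives 320 at minimum enrolment. For 20% vs 32.3%, power is then about 67-71%, not 80%, and the detectable difference is about 14 points, not 12. This rests only on the protocol's figures, and it holds under either reading of the two groups and in either direction.

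Second, the 12-point claim does not extend to depression and/or anxiety. With 30% in pooled controls and an assumed 42.3% in HCPs, power is about 70% even if 400 vs 125 is accepted, and about 60% at 320 vs 100.

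All figures use a pooled-variance test without continuity correction, which reproduces the plan's numbers; with the correction they would be lower. Figures for HCPs vs controls require the two control groups to be pooled.

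**What to change.** In the Abstract and under Sample Size:
- Base the follow-up power on the 40% response of the Follow-up study section: 320 HCPs, and 50 + 50 = 100 pooled controls.
- State which two groups are compared, and that the controls are pooled if so.
- For physical symptoms, restate power for 20% vs 32.3% as about 67-71%, or the detectable difference as about 14 points, giving the single value for the chosen comparison and direction.
- For depression and/or anxiety, give a separate figure: about 15.5 points at 320 vs 100 from a 30% base.
- Reduce n = 160 to 128 and restate the 15-point paired claim with its discordance assumption.
- Delete the sentence describing the assumptions as most conservative.

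In the End of Study Definition, reconcile the target of more than 400 in group 4 with the forecast of 320 at minimum enrolment, for example by stating that it presumes more than 1,000 recruited HCPs at 40% response. The 12-month backstop can stay.

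The cost is wording and a less favourable stated power. No extra participants and no change to the assessments are needed.

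### The 80% power for a 15% change is claimed for all objectives in 160 HCPs selected for anxiety or depression at baseline; it cannot hold for that composite or for the between-group objectives

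*Protocol article*

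**What the plan says.** The Sample Size section first sizes the baseline comparison at 40% against 30%. It then turns to follow-up: "Assuming that only 50% of these HCPs agree to be a part of a cohort survey (*n* = 400"). It takes 40% of these 400, giving 160 who reported depression or anxiety. The next claim, with alpha 0.05 two-sided, is about 80% power "to detect difference of 15% between baseline and the end-of study for all the primary and secondary objectives, amongst those who have reported anxiety"; the group meant is the 160 just derived, with either condition at baseline. It closes with: "In the other arm, we have enough power to detect smaller changes from baseline".

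Primary endpoint 2 is "Change in prevalence of combined anxiety and depression from baseline". The Method of Analysis section says: "We will evaluate for changes in proportion of those outcomes at baseline to the end of the study using paired McNemar test". The primary objectives compare patient-facing HCPs with participants in non-patient-facing roles, and secondary objective 5 compares HCPs in the United Kingdom with HCPs in other regions.

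**The concern.** The 160 are chosen for having the outcome whose change the sentence says it can detect. For the and/or composite the baseline proportion is therefore 100%, and a paired comparison with baseline can only show a fall. Some people always fall below a cut-off on re-measurement, so such a test would be significant whether or not mental health improved. If the other arm means the remaining 240 HCPs without symptoms at baseline, the same problem runs the other way: their prevalence starts at 0% and can only rise.

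The scope is also too wide. A change within one subset of HCPs says nothing about power to compare HCPs with controls, or one region with another. A reader who relies on the sentence would think that primary objective 2 has been powered when it has not.

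**Working it through.** **Inputs from the Sample Size section:** n = 160; d = 0.15; two-sided alpha 0.05; stated power about 80%. The baseline proportion and the share of discordant pairs, s, are not given.

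**1. What the stated 80% needs.** McNemar power, normal approximation: Φ[(d√n − 1.96√s) / √(s − d²)], with d√n = 0.15 × √160 = 1.897.

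| s | power |
|---|---|
| 0.15 (all one way) | 99.9% |
| 0.30 | 94.1% |
| 0.45 | 81.4% |
| 0.46 | 80.5% |
| 0.50 | 77.0% |

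At s = 0.46: (1.897 − 1.329) / √0.4375 = 0.859, so power is 80.5%. The stated figure is thus reproduced at about 46% discordance, which means changes in both directions (about 30% one way and 15% the other).

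**2. The and/or composite in the 160.** All are positive at baseline, so no one can become positive and s = d = 0.15. Exact power for a fall from 100% to 85% is P(X ≥ 6) with X ~ Bin(160, 0.15), which is above 99.9%. The exact two-sided p-value with k one-way pairs is 2 × 0.5^k: 0.0625 for k = 5 and 0.031 for k = 6. A true fall of only 5 points has 82% power.

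**3. Regression to the mean.** Assume 40% prevalence at both times, a bivariate-normal latent score and retest correlation r. The documents give no r.

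| r | of the 160, below cut-off at follow-up | of the 240, above it |
|---|---|---|
| 0.7 | 30.6% (49) | 20.4% (49) |
| 0.8 | 24.8% (40) | 16.5% (40) |
| 0.9 | 17.4% (28) | 11.6% (28) |
| 0.95 | 12.2% (20) | 8.2% (20) |

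Every count is far above the six needed for p < 0.05. The fall in the 160 reaches 15 points unless r exceeds roughly 0.92–0.93.

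**4. Who the other arm is.** The neighbouring figure of 20% against 32.3% gives 78–79% power at 160 vs 240 (400 − 160 = 240). That fits a comparison of HCPs with and without symptoms at baseline, but the text does not say so.

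**5. Between-group difference in change.** With common discordance s, the difference detectable with 80% power is about 2.80 × √[s(1/n₁ + 1/n₂)]. Two sizes are used:
- 400 vs 160, from the End of Study Definition, read as 80 in each of Groups 5 and 6.
- 320 vs 100, from the Follow-up study section: 60% agree and two-thirds of those respond, so 40% of 800 and of 250.

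Discordance in the model is 2 × 0.40 × the share falling below: 0.14 at r = 0.9 and 0.24 at r = 0.7.

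| s | 400 vs 160 | 320 vs 100 |
|---|---|---|
| 0.14 | 9.8 points | 12.0 points |
| 0.24 | 12.8 points | 15.7 points |
| 0.28 (r about 0.6) | 13.9 points | 17.0 points |

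**The case against.** The strongest reply is that the 160 appear only in the power text. The Method of Analysis section names McNemar for change from baseline but does not restrict it to people positive or negative at baseline, and endpoint 2 is unrestricted. A reader might infer that the study is bound to report improvement in symptomatic HCPs and worsening in the rest. The documents do not support that: such subset tests are suggested by the power sentence but not specified. This part of the reply stands.

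Three further limits also stand.
- The 100% baseline is exact only for the and/or composite. Endpoint 1 uses and/or, while endpoint 2 speaks of combined anxiety and depression. If endpoint 2 requires both conditions, the 160 do not all start positive and the test is not degenerate. Selection would still favour a fall, because every baseline positive lies inside the 160 while some follow-up positives may lie outside.
- Regression to the mean need not reach 15 points. That depends on an assumed correlation below about 0.92–0.93, and in the 240 the rise is under 15 points at r = 0.9.
- The target of 1050 does not rest on this sentence. The 40% vs 30% comparison at 800 vs 250 reproduces at 82.2%, so no shortfall in recruitment follows.

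The reply does not rescue the claim that the power applies to every primary and secondary objective.

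**Conclusion.** The power sentence is wrong in scope. For the anxiety and/or depression composite, about 80% for 15 points cannot hold in a subset that starts at 100%: the power is above 99.9%, and it is power to detect something that re-measurement alone would produce. This follows from the selection and needs no outside assumption. The size of the spurious change does need one: 12–31% in the 160 and, if they are the other arm, 8–20% in the 240, for assumed correlations of 0.95–0.7. The sentence gives no power for between-group or regional objectives.

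It would go too far to call the 80% an arithmetic error for every endpoint. For COVID-19 symptoms, sleep or burnout it is attainable at about 46% discordance; that input is simply not stated. Severity: should-fix, because a stated property of the design is wrong, but the analysis section does not commit the study to the faulty test.

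**What to change.** - Limit the n = 160 sentence and the one on the other arm to outcomes that do not define the subset. State the discordance assumed (about 46% for 80% power) and say who the other arm is.
- State that change in anxiety/depression prevalence is estimated in the whole follow-up cohort (Groups 4–6) and compared between groups, with no McNemar test against baseline inside subsets defined by baseline anxiety or depression.
- Report remission among those positive at baseline and new onset among those negative descriptively, with 95% confidence intervals.
- Replace the power figure with the detectable between-group difference in change and its discordance assumption: about 10–13 points at 400 vs 160 and 12–16 at 320 vs 100 for 14–24% discordance, or about 14 and 17 at 28%.

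The cost is wording and one clarified analysis; no new data are needed. A favourable-looking power statement is lost. Remission in the control groups will be imprecise: if 30% of about 80 are positive at baseline, each control group has about 24 cases.
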